## Abstract

**Background:**

This study aims to evaluate the effects of remote Baduanjin Qigong intervention on the quality of life and physical function in patients with mild to moderate Parkinson’s disease (PD) through a randomized controlled trial (RCT) and to compare its efficacy with conventional exercise rehabilitation.

**Methods/design:**

This RCT will enroll participants who, following baseline assessments and physical function tests, will be randomly allocated into one of three groups: the Qigong group (QG), the conventional exercise rehabilitation group (EG), or the control group (CG). The QG will engage in live-streamed Baduanjin (Eight-Section Brocade) sessions three times per week, each lasting 40 min, with additional self-practice encouraged. The EG will undergo a structured regimen consisting of moderate period high-intensity resistance training (MP-HI-RT) combined with moderate period low-intensity aerobic exercise (MP-LI-AE), also performed remotely in three 40-min sessions per week. The CG will continue their routine daily activities without additional exercise intervention. Outcome assessments will be conducted at baseline (Week 1), mid-intervention (Week 6), and post-intervention (Week 12) to evaluate both short-term and long-term effects. The primary outcomes include quality of life, evaluated using the Parkinson’s Disease Questionnaire-39 (PDQ-39), the MOS 36-item Short Form Health Survey (SF-36), and the Unified Parkinson’s Disease Rating Scale developed by the Movement Disorder Society Part I (MDS-UPDRS Part I). Secondary outcomes encompass reaction time, balance, physical coordination, flexibility, and walking capacity.

**Discussion:**

The importance of exercise rehabilitation for PD is increasingly recognized by doctors and patients. However, accessible and practical rehabilitation methods remain an area of active investigation. Remote Baduanjin Qigong intervention via the Internet offers a promising alternative for mild to moderate Parkinson’s disease patients.

**Clinical trial registration:**

https://www.chictr.org.cn/bin/project/edit?pid=268557, Identifier ChiCTR2500101461.

## Background

1

Parkinson’s disease (PD) is the fastest-growing age-related neurodegenerative disorder worldwide and ranks as the second most prevalent neurological condition after Alzheimer’s disease. Affecting more than six million individuals globally, PD significantly compromises quality of life, impacting both physical and mental well-being (1, 2). Without effective intervention, PD patients experience significant impairments in motor function, leading to a substantial decline in quality of life, characterized by symptoms such as sleep disturbances, speech impairments, and emotional disorders (3, 4). Although pharmacological treatment remains the primary approach for alleviating PD symptoms, its clinical application is often constrained by side effects, the development of drug resistance, high costs, and so on (5). In contrast, physical exercise, which is free from adverse effects, has demonstrated positive outcomes in the treatment of other neurodegenerative diseases (6–8). Consequently, increasing research has focused on exercise interventions as a non-pharmacological approach to mitigating PD symptoms.

Existing research has demonstrated that exercise interventions can alleviate key clinical symptoms of PD, including postural instability, muscle rigidity, tremors, and bradykinesia. Moreover, these interventions contribute to improvements in physical function, enhancing muscle strength and balance, while also exerting positive effects on non-motor symptoms such as mood and cognitive function (9–13). As a result, exercise interventions are now widely recognized as an integral component of comprehensive PD management (14, 15). However, conventional exercise interventions are often limited by factors such as transportation barriers (e.g., long travel distances, lack of accessible public transportation), time constraints and high costs, making it challenging for many patients to access professional exercise guidance and rehabilitation. In recent years, with the rapid advancement of modern internet technology, remote interventions for PD patients have emerged as a feasible solution (16–18).

Baduanjin Qigong is a mind–body exercise that integrates mental regulation, breathing techniques, and physical movement. It is developed based on ancient Chinese Qigong literature and must be certified by the Chinese Health Qigong Association (19). Previous research has shown that Baduanjin Qigong training not only strengthens core muscle groups and improves postural stability in PD patients but also alleviates anxiety, depression, and sleep disturbances, thereby significantly enhancing their quality of life (20–22). However, studies investigating the effects of remote Baduanjin Qigong interventions on symptom improvement in patients with mild to moderate PD remain limited. Furthermore, no conclusive evidence has established whether Baduanjin Qigong offers superior benefits compared to traditional exercise interventions, such as combined aerobic exercise and resistance training. Therefore, this study seeks to assess the effects of remote Baduanjin Qigong intervention on the quality of life and physical function of patients with mild to moderate PD through a randomized controlled trial (RCT) with comparative analysis.

## Objectives

2

To assess the feasibility and effectiveness of Internet-based remote intervention as a practical approach for exercise rehabilitation in individuals with PD.To determine whether remote Baduanjin Qigong intervention enhances quality of life and physical function in patients with mild to moderate PD.To compare the therapeutic effects of remote Baduanjin Qigong intervention with those of conventional exercise rehabilitation (aerobic and resistance training) in alleviating clinical symptoms and improving functional outcomes in PD patients.

## Design and methods

3

### Design

3.1

This study is a 12-week randomized controlled trial (RCT). Participant recruitment will be initiated in June 2025, and data analysis will be conducted once the required sample size has been achieved. The study design flowchart is presented in Figure 1.

**Figure 1 fig1:**
[figure not shown]
The flow chart of the trial design.

### Subject recruitment

3.2

#### Inclusion criteria

3.2.1

Diagnosis of PD based on the Hoehn & Yahr staging system (Stages I–II).Male or female patients aged between 50 and 80 years.Currently receiving stable anti-Parkinsonian medication, with no changes in the treatment regimen for at least 3 months.Basic self-care ability with no severe cognitive impairment (Mini-Mental State Examination [MMSE] score ≥24).Ability to follow simple instructions and absence of uncontrolled chronic diseases.Able to safely walk independently for at least 500 feet without an assistive device.No prior experience with Baduanjin Qigong practice and willingness to sign an informed consent form.

#### Exclusion criteria

3.2.2

Prior experience with systematic Baduanjin Qigong training or resistance exercise programs.Severe cardiovascular disease, musculoskeletal disorders, or other conditions that significantly impair physical activity.Severe mental illness or cognitive dysfunction (MMSE score <24).Recent deep brain stimulation (DBS) treatment.Inability to access the internet for remote training.

#### Dropout criteria

3.2.3

Disease progression during the study period (e.g., advancement to Hoehn & Yahr Stage III).Serious adverse events (e.g., falls resulting in fractures).Inability to continue the intervention for any reason or voluntary withdrawal from the study.

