### Qigong group (QG)

3.6

Participants in the Qigong group will practise Baduanjin (Eight-Section Brocade) through live-streamed video sessions under the guidance of professional instructors. Baduanjin is a traditional mind–body exercise that integrates physical movement, breath control, and psychological regulation. It consists of eight sequential movements, primarily involving upper and lower limb coordination, head–neck control, and spinal movement, all performed in synchronisation with rhythmic breathing. Each complete session will last approximately 10 to 15 min. During the first week, participants will receive systematic instruction sessions in small groups (five participants per group, with a total of ten groups) via a two-way live video conferencing platform. Certified Qigong instructors will guide participants step by step through the eight standard Baduanjin movements so that all participants can master the basic forms and key techniques. Instructors will closely monitor each participant’s postures, breathing techniques, and movement sequences, providing real-time corrections and movement modifications when needed. This real-time, two-way format will consistently be applied in all remote sessions during the intervention period to guarantee correct practice and optimize training effectiveness. From week 2 onward, participants will engage in three 40-min remote sessions per week, which included 5 min of warm-up, 30 min of core Baduanjin practice, and 5 min of cool-down exercises under professional supervision. Participants will also be encouraged to practice independently outside of the scheduled sessions to enhance training effectiveness. Participants who withdrew from the study will be asked to provide their reasons for discontinuation.

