### Control group (CG)

3.8

Participants in the control group will not receive specific exercise guidance and will be instructed to maintain their usual daily activities. Researchers will conduct regular monthly follow-ups to assess participants’ status and to confirm that they do not engage in additional exercise interventions during the study period.

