### Data collection and management

3.16

To ensure the accuracy and reliability of data collection, all personnel responsible for data measurement and recording underwent standardized training on operational procedures. Data monitoring will be conducted by independent personnel who are not involved in the intervention of the study. This process will include reviewing all informed consent forms, verifying data integrity, and cross-checking source documents. All data will be collected at three time points (Week 1, Week 6, Week 12) to monitor short-term and long-term effects. Data will be recorded on standardised report forms and transferred to a web-based data management system (REDCap) through multiple secure entries. Any errors identified during data entry will be corrected, with the researcher providing a signature and date for verification. Participants will have the right to withdraw from the study at any time, for any reason. In cases of withdrawal, data already collected will remain in the dataset unless the participant requests removal.

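### The dropout criteria do not separate stopping the intervention from leaving the study, so Week 6 and Week 12 data may be lost in a way related to outcome and partly to arm

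*Protocol article*

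**What the plan says.** Section 3.2.3 (Dropout criteria) has three items:

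- "Disease progression during the study period (e.g., advancement to Hoehn & Yahr Stage III"), an example one stage beyond the Stage I–II entry range;
- "Serious adverse events (e.g., falls resulting in fractures");
- "Inability to continue the intervention for any reason or voluntary withdrawal from the study", which puts stopping the intervention and leaving the study in a single item.

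What happens afterwards is described in two places. Sections 3.6 and 3.7 (QG and EG) carry the same sentence: "Participants who withdrew from the study will be asked to provide their reasons for discontinuation". Section 3.16 adds: "In cases of withdrawal, data already collected will remain in the dataset unless the participant requests removal". Neither mentions later visits.

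For the control arm, section 3.8 says: "Participants in the control group will not receive specific exercise guidance and will be instructed to maintain their usual daily activities". Outcomes are measured at Weeks 1, 6 and 12 (sections 3.12 and 3.13). Section 3.17 makes a mixed-effect model with baseline adjustment the main analysis and also foresees one-way ANOVA or Kruskal-Wallis tests at single time points. Section 3.19 allows for 15% dropout in each of the three groups.

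**The concern.** A randomised comparison is protected only while outcomes are obtained from everyone randomised, whatever treatment they go on to receive. Here the list of reasons for exit works against that in two ways.

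First, two of the triggers are bad outcomes, or close to them. Progression and a fracture bear on quality of life, balance and walking, which the trial sets out to measure. Removing participants when these occur removes poor results selectively.

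Second, part of the third trigger depends on arm. CG has no exercise programme that a participant could become unable to continue, so in practice that route out is open only in QG and EG.

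With only three visits, a deterioration after Week 6 that leads to exit leaves no trace in the recorded data, and someone who leaves before Week 6 contributes baseline only. A later analysis plan can choose how to handle missing values, but it cannot recover assessments that were never made. The matter therefore belongs in the protocol and is not a detail that can be left to the analysis plan.

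**Working it through.** **Inputs from section 3.19.** SD 10.5, target difference 5 PDQ-39 points, dropout 15%, 50 per group. The plan's inflation step reproduces: 42 / (1 − 0.15) = 49.4, so 50 per group and 150 in total. After 15% loss, 50 × 0.85 = 42.5 per group remain. The base of 42 is a separate matter and is not relied on here.

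**Assumptions.** The document does not give the share lost by arm, how much worse those lost would have fared, or the correlations below. All of these are assumed.

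**Check 1: simple shift.** Let those lost be worse than those retained by D points, with shares lost p_E (exercise arm) and p_C (control). Each arm's retained mean is then better than its full mean by p × D, so the between-group difference shifts by (p_E − p_C) × D in favour of exercise.

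| p_E | p_C | D = 5 | D = 10 |
|---|---|---|---|
| 0.15 | 0.15 | 0 | 0 |
| 0.15 | 0.05 | 0.5 | 1.0 |
| 0.20 | 0.05 | 0.75 | 1.5 |
| 0.15 | 0 | 0.75 | 1.5 |

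If loss is greater in CG than in the exercise arm, the sign reverses.

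**Check 2: one-sided extreme, those retained only.** Let 15% of an exercise arm be lost and no controls. Let dropout propensity correlate ρ with the Week 12 outcome. Then the shift is ρ × SD × φ(z) / (1 − p), with z = 1.036 and φ(z) = 0.233. This gives ρ × 10.5 × 0.233 / 0.85 = ρ × 2.88:

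- ρ = 0.3: 0.86 points
- ρ = 0.5: 1.44 points
- ρ = 0.7: 2.02 points

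Against the 5-point target this is 17% to 40%.

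**Check 3: the same extreme, using earlier visits.** The mixed model uses each lost participant's retained visits. I simulated the scenario of Check 2, predicting the missing Week 12 values from baseline and Week 6, with an assumed equal correlation r between visits. The remaining bias, in points to within a few hundredths, is about:

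| | ρ = 0.3 | ρ = 0.5 | ρ = 0.7 |
|---|---|---|---|
| r = 0.7 | 0.37 | 0.65 | 0.94 |
| r = 0.5 | 0.56 | 0.98 | 1.41 |

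As a rough cross-check, two earlier visits explain 2r²/(1 + r) of the Week 12 variance. This leaves 0.42 unexplained at r = 0.7 and 0.67 at r = 0.5. For ρ = 0.3, 0.86 × 0.42 = 0.36 and 0.86 × 0.67 = 0.58, in line with the table.

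If exit comes before Week 6 and only baseline is available, the bias over the same cases is about 0.45 to 1.56. If CG also loses 7.5%, the values with both visits fall to about 0.17–0.44 (r = 0.7) and 0.26–0.65 (r = 0.5).

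**The case against.** The strongest objection is that the article never says assessments stop when a criterion is met. The sentence in section 3.16 follows a statement of the right to withdraw and assures that withdrawers' data are retained. It does not say that only those data will exist, and the full protocol may provide for further visits. This stands as a limit. The conclusion rests on the heading of section 3.2.3, on its pairing of stopping the intervention with withdrawal, and on sections 3.6, 3.7 and 3.16 describing nothing beyond asking for reasons and keeping earlier data. Someone running the trial from this text would reasonably stop the visits.

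A reader might infer that Week 12 compares the remaining exercisers with all controls. The document does not support that. The criteria apply to every arm, controls can leave through progression, serious events or withdrawal, and section 3.19 plans the same 15% in each group. Nor does poor adherence alone remove anyone, since section 3.10 answers it with extra guidance and family support.

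A reader might also take the shifts in Check 2 as the expected bias, or convert them into a type I error. With SE = 10.5 × √(1/42.5 + 1/50) = 2.19, they would imply two-sided rejection rates of about 7%, 10% and 15% with no true effect. The arithmetic is right, but it describes an unadjusted mean of those retained with no loss in CG. That is closer to the single-time-point tests in section 3.17 than to the baseline-adjusted mixed model that is its main analysis. These figures are an upper illustration only.

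Finally, analysis sets and sensitivity analyses commonly sit in an analysis plan. Their absence here is not part of this point.

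**Conclusion.** The point holds as a fault in the stated rule. As written, stopping the intervention reads as leaving the study, and the reasons for exit are related to the outcomes and in part to the arm. The mixed model removes the resulting bias only so far as baseline and Week 6 values explain who is lost, which is doubtful when the triggering event falls between visits.

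The comparisons of QG and EG with CG could therefore be biased. Neither size nor direction can be derived from the document. On assumed values the bias is about zero when loss is equal and similar across arms. It is roughly 1 to 2 points in one-sided extremes at the stronger assumed correlations if only those retained are compared, and about 0.4 to 1.4 points in the same extremes once both earlier visits are used. If progression removes mainly controls, the bias runs against exercise. The change is worth making because it is cheap and the lost data cannot be recovered later. Confidence is moderate, because the ending of assessments is inferred and not stated.

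**What to change.** In section 3.2.3, list reasons for discontinuing the intervention separately from withdrawal of consent to follow-up. State that every randomised participant keeps the scheduled Week 6 and Week 12 assessments unless they refuse further follow-up, and stays in the randomised group for analysis. Questionnaires can be completed remotely, and physical tests done only where safe. Align the sentences in sections 3.6, 3.7 and 3.16 with this distinction. If continued assessment is already intended, one clarifying sentence is enough.

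The cost is a wording change and some extra effort to follow about 22 participants (15% of 150 = 22.5) at visits that are already scheduled. The change takes no position on when exercise should stop.

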#### Recruiting methods

3.2.4

This study aims to recruit 150 eligible participants from the Beijing region through referrals from neurologists and PD specialists at major tertiary hospitals and movement disorder clinics. Specialists will briefly introduce the study to potential patients and their families. If patients express interest, the research team at Beijing Sport University will then contact them directly by phone, email, or message to complete eligibility screening and obtain informed consent. Recruitment will also be supported by advertisements in local newspapers, television, and reputable online platforms. To minimise gender bias and ensure the generalisability of the findings, efforts will be made to recruit an approximately equal number of male and female participants (50/50 ratio) whenever possible. The recruitment process will follow these steps:

Develop a recruitment plan and confirm participant sources.Screen interested patients based on inclusion and exclusion criteria, including review of medical records, diagnostic certificates, or other documentation issued by PD specialists at tertiary hospitals or movement disorder clinics, along with medical history information provided by the patient or their family.Establish procedures for contacting participants, including preparing relevant data, videos, and images to facilitate participants’ understanding of the study objectives.Develop procedures for obtaining informed consent, ensuring that participants or their legal guardians sign the consent form.

### Subject grouping

3.3

All participants will receive a comprehensive explanation of the study’s objectives, procedures, potential benefits, and possible risks before the trial. They will voluntarily sign an informed consent form and will be informed that they can withdraw from the study at any stage without any adverse consequences. After completing the informed consent process, participants will be randomly assigned in a 1:1:1 ratio to one of three groups—the Qigong group (QG), the conventional exercise rehabilitation group (EG), or the control group (CG)—using a computer-generated random number table. Participants in both the Baduanjin Qigong and conventional exercise rehabilitation groups will receive three remote live training sessions per week and will be encouraged to perform an additional two to three self-guided sessions weekly. Participants in the control group will maintain their usual daily activities without additional exercise intervention, but will be required to complete regular follow-ups and assessments.

### Allocation

3.4

#### Allocation concealment mechanism

3.4.1

To prevent selection bias, the researcher responsible for generating the randomization sequence will be independent from those determining participant eligibility. The randomized sequence will be generated using a computer-generated block randomization (SPSS 26.0) and will be stored by a research manager who will not be involved in the intervention or assessment process. Each allocation will be sequentially numbered and placed in an opaque, tamper-proof, and light-tight envelope. These envelopes will be securely sealed and stored by an independent research coordinator. Only after an eligible participant had completed baseline assessments and formally agreed to participate will the next envelope in sequence be opened by the research coordinator to reveal the intervention assignment. Neither the participants nor the interventionists will be aware of the allocation until the envelope is opened, ensuring strict allocation concealment.

### Implementation

3.5

After completing baseline evaluations and physical function tests, participants will be randomized in a 1:1:1 ratio to one of the three groups: the Qigong group (QG), the conventional exercise rehabilitation group (EG), or the control group (CG). The research coordinator will open the next sealed envelope in sequence to reveal each participant’s assignment.

### Qigong group (QG)

3.6

Participants in the Qigong group will practise Baduanjin (Eight-Section Brocade) through live-streamed video sessions under the guidance of professional instructors. Baduanjin is a traditional mind–body exercise that integrates physical movement, breath control, and psychological regulation. It consists of eight sequential movements, primarily involving upper and lower limb coordination, head–neck control, and spinal movement, all performed in synchronisation with rhythmic breathing. Each complete session will last approximately 10 to 15 min. During the first week, participants will receive systematic instruction sessions in small groups (five participants per group, with a total of ten groups) via a two-way live video conferencing platform. Certified Qigong instructors will guide participants step by step through the eight standard Baduanjin movements so that all participants can master the basic forms and key techniques. Instructors will closely monitor each participant’s postures, breathing techniques, and movement sequences, providing real-time corrections and movement modifications when needed. This real-time, two-way format will consistently be applied in all remote sessions during the intervention period to guarantee correct practice and optimize training effectiveness. From week 2 onward, participants will engage in three 40-min remote sessions per week, which included 5 min of warm-up, 30 min of core Baduanjin practice, and 5 min of cool-down exercises under professional supervision. Participants will also be encouraged to practice independently outside of the scheduled sessions to enhance training effectiveness. Participants who withdrew from the study will be asked to provide their reasons for discontinuation.

